### Sample size considerations

We designed the trial in collaboration with the Department of Clinical Research of University Hospital in Basel as an event-driven trial to show the superiority of continued nutritional therapy for patients discharged from the hospital compared with usual care regarding mortality. The sample size was calculated for the Swiss cohort only. We targeted 247 mortality events and a total sample size of at least 802 participants, who are assigned 1:1 to nutritional therapy and the usual care groups. We hypothesised an incidence of mortality of 20% per year in the usual care group, an effect estimate of 0.7, a type I error rate of 0.05, a power of 80%, a recruitment period of 1.5 years, a trial duration of 3 years and a withdrawal rate of 10% per year of follow-up.

Additionally, we calculated the required sample size for several different assumptions regarding the effect of our intervention, study durations and recruitment periods. Assuming an HR of only 0.75 and a power of 80%, the required sample size would be 1200. Thus, we recruit at least 802 participants but can continue to reach a maximal total of 1200 patients depending on timing/success of recruitment. Figure 5 demonstrates effect size estimations for the number of events needed in the trial.

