**Methods and analysis:**

The *Effect of Continued Nutritional Support at Hospital Discharge on Mortality, Frailty, Functional Outcomes and Recovery* (EFFORTII) is an investigator-initiated, non-commercial randomised controlled trial designed to evaluate whether ongoing, individualised nutritional therapy after hospital discharge—targeted to meet specific energy and protein requirements—offers a cost-effective approach to lowering mortality, minimising complications and maintaining functional status compared with standard care. Eligible participants are adult, chronically ill medical inpatients at risk of malnutrition. Patients in the intervention group receive individualised nutritional therapy delivered by an experienced dietitian through a combination of telemedicine and in-person consultations. The intervention aims to meet personalised nutritional targets, supported by a trained dietitian. Control group patients receive nutritional counselling at discharge, but no structured nutritional management during follow-up. We designed the trial as an event-driven trial with a target of 247 mortality events (primary endpoint), which will be assessed over approximately 5 years until event-driven endpoint is met. The minimum total sample size is at least 802 participants, based on the assumed treatment HR of 0.70. The main trial is enrolling patients across multiple sites in Switzerland. During the trial, additional sites in Spain joined the study, and their data will be analysed using a patient-level pooled approach.

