### Study endpoints

All patients in both groups are contacted every 6 months by structured phone calls from a blinded study nurse or dietitian to assess primary and secondary endpoints until the patient reaches the primary endpoint, drops out or until the study is terminated. If necessary, information on patient mortality, rehospitalisations or major complications during the follow-up period is confirmed through family members or the patient’s primary care physician.

The primary endpoint is defined as the time from trial inclusion to death from any cause (ie, all-cause mortality). Secondary endpoints are defined as:

Time to non-elective hospital readmission after discharge from the index hospital stay.Time to the first major complication including death, bacterial infection with need for antibiotic treatment, major cardiovascular event (ie, stroke, intracranial bleeding, cardiac arrest, myocardial infarction) or pulmonary embolism, acute renal failure, gastro-intestinal events (including haemorrhage, intestinal perforation, acute pancreatitis).Changes in functional status measured by the Barthel’s index (scores range from 0 to 100, with higher scores indicating better functional status).^25^Changes in quality of life measured with the EQ-5D index (German Version, EQ-5D index values range from 0 to 1, with higher scores indicating better quality of life) including the VAS (EQ-5D VAS) (scores range from 0 to 100, with higher scores indicating better health status).

We will follow participants until the end of the study, ie, until approximately 247 mortality events have occurred. We expect a maximum follow-up period of 5 years for patients enrolled at the start of the study. In addition to blinded telephone follow-up examinations, the unblinded study dietitian conducts home visits or in-clinic at 3, 6 and 12 months for all patients to evaluate the study-specific nutritional outcomes.

Body weight.Calf circumference to assess muscle mass.Bioelectrical impedance analysis to assess body composition (fat-free mass, fat mass).Hand grip by means of handgrip strength through dynamometry (Jamar Hydraulic Hand Dynamometer) to assess muscle strength.^26^

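### Enrolling up to 1200 patients adds no primary-test power at HR 0.75 while the study ends at about 247 deaths: power stays near 62%

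*Protocol article*

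**What the plan says.** The sample size section of the Protocol article sets the main target: "We targeted 247 mortality events and a total sample size of at least 802 participants", for HR 0.70 with 80% power, Swiss cohort only. It then reports a second scenario: "Assuming an HR of only 0.75 and a power of 80%, the required sample size would be 1200". The next sentence draws the consequence for enrolment: "Thus, we recruit at least 802 participants but can continue to reach a maximal total of 1200 patients depending on timing/success of recruitment".

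The end of the study is defined in two places, both by the same number of deaths. Study endpoints: "We will follow participants until the end of the study, ie, until approximately 247 mortality events have occurred". Abstract, Methods and analysis: "event-driven trial with a target of 247 mortality events (primary endpoint), which will be assessed over approximately 5 years until event-driven endpoint is met". Neither place gives a different number for an extended trial, and the sample size section names no event target other than 247.

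The primary test is a log-rank test on Swiss patients, and no interim analysis is planned (Statistical approach). The caption of Figure 5 notes that the number of deaths needed depends on the true HR.

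**The concern.** The HR 0.75 scenario is the only reason the article gives for setting the ceiling at 1200. A reader will take the extension as protection against an effect smaller than planned. In an event-driven trial that protection comes from more deaths, and the stopping rule allows no more deaths at 1200 patients than at 802. The justification for 1200 and the rule that ends the study therefore do not fit together.

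At stake is what the sponsor, funders and readers believe about the trial's sensitivity. If the true HR is 0.75, a 247-death analysis misses it about 38% of the time, not 20%. A non-significant result after enrolling 1200 could then be read as stronger evidence against an effect of that size than it is.

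**Working it through.** **Inputs**, all from Sample size considerations: "We hypothesised an incidence of mortality of 20% per year in the usual care group"; "a recruitment period of 1.5 years, a trial duration of 3 years and a withdrawal rate of 10% per year of follow-up"; HR 0.70 or 0.75; type I error 0.05; power 80%; 1:1 allocation. The article does not say whether the test is one- or two-sided. I take it as two-sided because only that reproduces 247 (one-sided 0.05 would need 195 deaths).

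**Step 1. Deaths required (Schoenfeld).** d = 4(1.960 + 0.842)² / (ln HR)² = 4 × 7.849 / (ln HR)².
- HR 0.70: 31.40 / 0.12722 = 246.8, so 247. This matches the article.
- HR 0.75: 31.40 / 0.08276 = 379.4, so 380.

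Freedman's formula gives 253 and 385, so the gap does not depend on the formula.

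**Step 2. Patients required.** Take exponential survival with control hazard λ = −ln 0.8 = 0.2231 and withdrawal hazard η = −ln 0.9 = 0.1054, uniform accrual over R = 1.5 years and total duration T = 3 years. With s = λ + η, the probability of an observed death in one arm is

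p = (λ/s) × [1 − (e^(−s(T−R)) − e^(−sT)) / (sR)].

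The intervention arm uses HR × λ.

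| HR | p control | p intervention | mean p | deaths needed | N = deaths / mean p | N in article |
|---|---|---|---|---|---|---|
| 0.70 | 0.352 | 0.264 | 0.308 | 247 | 804 | 802 |
| 0.75 | 0.352 | 0.279 | 0.315 | 380 | 1205 | 1200 |

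Taking withdrawal as a rate of 0.10 instead gives 799 and 1199. Both of the article's sample sizes therefore reproduce closely. The 1200 does so as the number that yields about 1200 × 0.3154 = 378 deaths when everyone is followed to 3 years.

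**Step 3. Power when the cut-off is at 247 deaths.** Power = Φ(√d / 2 × |ln HR| − 1.960).
- HR 0.70: Φ(7.858 × 0.3567 − 1.960) = Φ(0.843) = 80.0%.
- HR 0.75: Φ(7.858 × 0.2877 − 1.960) = Φ(0.301) = 61.8% (Freedman 61.2%).
- HR 0.75 with 380 deaths instead: Φ(9.747 × 0.2877 − 1.960) = Φ(0.844) = 80.1%.

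N does not enter the formula, so 61.8% applies to 802 and to 1200 alike. The shortfall is 380 − 247 = 133 deaths, or 54% of 247.

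**Step 4. Check by simulation.** Log-rank tests with the data cut at the 247th death, HR 0.75, control hazard 0.20 per year, withdrawal 10% per year, 4000 runs each:

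| Accrual | N = 802 | N = 1200 |
|---|---|---|
| 1.5 years | 61.2% | 60.4% |
| 4 years | 60.6% | 60.8% |

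With 1.5-year accrual, the larger trial reached the 247th death at about 2.2 years instead of 3.2, with no gain in power.

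**The case against.** **The article does not say outright that 1200 patients give 80% power.** This stands as far as it goes. The text says what sample size would be needed at HR 0.75, as one of several scenarios, and the link to the ceiling is the single connective that opens the next sentence. The extension is also tied to how recruitment goes, which fits an operational reading. A reader might infer that the article claims 80% power at HR 0.75 for the design as run; it implies this and does not assert it. But no other reason for 1200 is offered, and under the operational reading the HR 0.75 figure has no role.

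**The full protocol or the statistical analysis plan may set a higher target.** That is possible, and the Figure 5 caption shows awareness that smaller effects need more deaths. But the point is not a missing detail: the article states 247 deaths as the end of study twice, without exception.

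**The stopping rule is approximate, and sidedness is unstated.** A small overshoot does not cover 133 deaths. A one-sided 0.05 test would give 73% at HR 0.75, still short of 80%.

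**More patients are not useless.** Agreed. They can improve precision for the repeated functional and quality-of-life measures and for the nutritional measures at 3, 6 and 12 months. The finding concerns only the primary test.

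**Shortened follow-up.** A reader might also infer that the extension would cut follow-up drastically. At the planned pace (802 in 1.5 years, so 1200 in about 2.25) and HR 0.70, last-patient follow-up would fall from 18 months to about 3. The documents do not support this as the trial's actual consequence. Study design and setting says recruitment began in 2021 and that Swiss sites had 80% of planned patients when Spain joined in 2024. If that means 80% of 802 in about 3 years (an assumption), 802 patients take about 3.75 years and the 247th death falls at about 4.3 years. Last-patient follow-up is then about 6 months even without an extension.

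**Conclusion.** The point holds as an inconsistency between the article's own figures. The ceiling of 1200 rests on about 380 deaths, while the study ends at about 247. Under that rule, primary-test power at HR 0.75 is about 62%, not 80%, with 802 or 1200 patients.

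This assumes a two-sided 0.05 log-rank test, 1:1 allocation, proportional hazards and a cut-off close to 247 deaths. It does not depend on accrual pace, control mortality or withdrawal, which affect only when the 247th death occurs. The Spanish patients do not change it, because the primary analysis and the sample size are Swiss only.

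It would be wrong to conclude that the trial is underpowered as declared: 247 deaths do give 80% power at HR 0.70. Nothing here touches the type I error or the choice of test.

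**What to change.** In Sample size considerations, keep 247 deaths and change the text on the extension in three ways:
- no longer offer 1200 patients as the route to 80% power at HR 0.75 under the 247-death rule;
- state that power at HR 0.75 with 247 deaths is about 62%;
- say that enrolment beyond 802 only shortens the time to 247 deaths.

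This costs a few sentences and a less favourable stated power. Nothing in the conduct of the trial changes.

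If the sponsor does intend 80% power at HR 0.75, the article must instead state a cut-off of about 380 deaths for the extended trial, in the abstract and in Study endpoints as well, and record that it was fixed without data by arm. That means waiting for about 133 more deaths and following patients longer. It is a real design change in a trial that has been recruiting since 2021, and the choice is the sponsor's.

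Any figures on shortened follow-up should be left out or labelled as illustrative of the planned accrual pace.

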**Figure 5 F5:**
[figure not shown]
The number of events required is dependent on the true HR between the control and intervention groups. The required number of events for achieving a power of 80% as a function of the true HR. The curves for a power of 70% and 90% (ie, 0.7 and 0.9) are also shown.

For the Spanish cohort, a convenience sample of 180 patients, 20–40 patients in each of the six recruitment sites, was defined. While this sample size does not provide adequate power for within-cohort mortality analyses, its inclusion alongside the Swiss cohort will enhance the overall statistical power of the pooled analysis and may provide insights into aspects of external validity.

## Discussion

Disease-related malnutrition remains a highly prevalent and clinically significant concern among polymorbid medical patients, leading to increased morbidity, greater functional impairment and elevated mortality rates following hospital discharge.^2^ While prior inpatient trials such as EFFORT^32^ and NOURISH^18^ demonstrated that structured nutritional therapy can improve short-term outcomes, the sustainability of these effects beyond hospitalisation has remained uncertain. EFFORTII is designed to fill this knowledge gap by evaluating whether ongoing, personalised nutritional therapy after hospital discharge can lower long-term mortality and enhance functional recovery compared with usual care. We submit that EFFORTII will be the largest outpatient nutritional RCT to date and will provide robust evidence on whether medical patients at nutritional risk show a sustained benefit from long-term nutritional therapy after hospital discharge. Additionally, it is designed to elucidate the mechanisms by which such therapy influences the course of disease from a physiopathological perspective. Towards this aim, we have planned several secondary projects with the created data base focusing on mechanistic research questions. To support this objective, a dedicated biobank has been established as part of the clinical trial. Blood samples are collected at the main study centre in Aarau and stored for future analyses, enabling the identification and investigation of potential biomarkers. This resource will facilitate subsequent mechanistic research projects and allow emerging scientific insights to be explored through additional, later-stage analyses.

The strengths of this protocol include its pragmatic, multicentre, randomised design, its large sample size and its sequential two-cohort strategy, which allows both regional evaluation and pooled international estimates. By targeting multimorbid patients at nutritional risk, the trial focuses on a prevalent and high-risk group in which the potential for benefit is greatest. Furthermore, the comprehensive set of secondary outcomes, including readmissions, complications, functional capacity, quality of life and nutritional parameters, will provide a multidimensional assessment of the intervention’s impact. The inclusion of parameters that evaluate body and muscle composition (such as BIA and calf circumference), as well as muscle function (handgrip strength), functional status (Barthel Index) and quality of life (EQ-5D), may help identify patients at greater risk of complications and guide future personalised therapeutic strategies beyond body weight or BMI.^33^ Further, by incorporating pharmaco-economic research, EFFORTII will elucidate the indications in which nutritional therapy is cost-effective. Thus, EFFORTII will facilitate a more efficient healthcare resource distribution.

An important innovation of EFFORTII is the extension of individualised nutritional therapy into the vulnerable post-discharge period. This is a phase in which patients often experience persistent anorexia, inflammation and functional limitations, yet outpatient nutritional management remains fragmented and rarely standardised.^23^ If successful, EFFORTII would provide high-quality evidence to support updating current ESPEN^21^ and ASPEN^22^ guidelines, which currently offer only weak guidance for outpatient nutritional therapy due to the lack of large randomised evidence.

The EFFORT research team has a broad and established network of national and international partners and extensive experience in conducting nutrition RCTs. This ensures the quality of the implementation and the achievement of the recruitment target. Furthermore, the target group of polymorbid patients is likely to represent a large group of people, which enhances the generalisability of the results and reflects real-world clinical practice. Nevertheless, we are aware of certain limitations of this trial. First, due to the design of the intervention, it is not possible to blind patients or caregivers to their randomisation, which could lead to bias. In addition, bias may occur if caregivers feel compelled to motivate patients in the control group to eat more. Nevertheless, outcome assessments can be conducted in a blinded manner via structured telephone calls from a study nurse. Second, non-adherence to nutritional interventions in the outpatient treatment over a period of 1 year and longer is possible due to differences in motivation, comorbidities or social support, which may influence effectiveness. The trial mitigates this by frequent contact with the study dietitians and individual planning, but some residual non-adherence or lost-to-follow-up is likely.

In conclusion, this pragmatic research project is planned to improve the quality, effectiveness, safety and efficiency of nutritional therapy in the outpatient setting. It will also help us to better understand the relationship between nutrition and illness in the long term. Data acquired through EFFORTII will thus help healthcare professionals and payers worldwide to make better-informed decisions regarding the best care of polymorbid individuals after acute illness, who represent a large and growing patient population worldwide, and one that accounts for a major share of medical resource consumption.
